**Figure 1 F1:**
[figure not shown]
Study design.

This study has been approved by the Research Ethics Committee of the Universitas Padjadjaran, Indonesia (No.1455/UN6.KEP/EC/2019) and has been registered in Thailand Clinical Trials Registry (TCTR; Identifier: TCTR20200530001). Protocol amendments will be updated in the trial registry (TCTR) so the study can be examined by any other parties.

### The Mobile-Based Counseling Application: SAENA

The application was developed in four major steps as follows: First, the application and a counseling protocol were developed. The application facilitates the helping relationship between the students and the counselors through written texts, voice calls, and video calls. These three communication modes can be used interchangeably during counseling sessions. The counseling protocol was developed based on the solution-focused brief therapy (SFBT) approach (Bavelas et al., 2013). The approach is effective in a lot of contexts (Kim, 2008; González Suitt et al., 2016), except for complex psychological problems (Chaudhry and Li, 2011). As a result, in the study, the participants will be screened using the Patient Health Questionnaire (PHQ-9) to exclude those with severe depressions. Second, the professionals who will perform the counseling were trained in using the application. However, the counselors need to have a prior experience in conducting micro-skills in a face-to-face counseling context. Third, a feasibility study was conducted. Based on this study, several improvements were made in the application and the protocol. Finally, the protocol of the non-inferiority trial was developed.

### Participants

The target population in the study will be University students who have academic-related psychological problems. The inclusion criteria of the sample are a University student, aged 18–25 years old, having academic-related problem(s), and registering as a participant in this study. The academic-related problems that will be included in the study are (1) (educational) adjustment difficulties; (2) difficulties in writing a thesis; (3) academic procrastination; (4) poor self-regulation for learning; and (5) a low grade point average (GPA). The study will exclude students with (1) physical disabilities; (2) under the care of mental health professionals; and (3) the score of PHQ-9 more than 14 (having severe depression), (Rahmadiana et al., 2019).

The participants of the study will be those who register in a University counseling center. They will be then screened with the PHQ-9. If they are willing to participate in the study, the research assistants will give informed consent and the right to withdraw from the study at any given time they wish to. The students who decline to join the study or withdraw from the study will be followed up to identify their reasons for declining and withdrawing from the study. The students have a right to undergo post-trial treatment if needed.

The sample size is a sensitive issue in the non-inferiority trial (Hahn, 2012). Large sample size is usually needed. However, if the new intervention is assumed to be slightly more effective than the TAU, the number of samples can be reduced. The mobile-based counseling application can be assumed to be more practical for the students in this country. Those who live remotely can still access the psychological services. The data from the University counseling center in 2020 were also a source of consideration in determining the sample size. The center admitted 482 clients in that year, with an average of 40 clients per month. With 80% CI, the expected SD will be one, and the inferiority margin (Δ) will be 0.24. It was calculated that the number of participants per arm needs to be 215 and the total sample size needs to be 430.

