### Outcome Measurements

The participants in the intervention group will complete the assessments at (1) the baseline (T0); (2) at the end of the first counseling session (T1); (3) at the end of the second counseling session (T2); (4) at the end of the third counseling session (T3); and (5) 3 months after the third counseling session (T4). There will be a week interval between the counseling sessions (T1, T2, and T3). Meanwhile, the participants in the control group will be measured at 3–5 points in time depends on the number of counseling sessions they have. They will fill the questionnaires at (1) the baseline (T0); (2) at the end of their counseling session(s), (T1 and/or T2 and/or T3, etc.); and (3) 3 months after the last session (TX). The data will be collected using the online forms and will be assisted by the research assistants.

The primary outcome of the proposed study will be CSE measured by the Coping Self-Efficacy (CSE) Scale. The Indonesian version of the CSE consists of 26 items with 11-point scale (0–10). The scale has good reliability (*r* = 0.92), (Nurhidayah, 2020). The total score will be used as an indicator of the level of CSE of participants. The CSE is defined as a belief about own ability of an individual to perform specific coping behavior (Chesney et al., 2006). Self-efficacy serves as evidence in measuring changes in the coping ability of individuals, especially for those who seek professionals to solve their problems (Chesney et al., 2006; Yoo et al., 2020).

The secondary outcomes of this study will be (1) resilience and (2) level of depression. Resilience is defined as the capacity of a dynamic system to adapt successfully to adversity that threatens system function (Masten, 2014). The Resilience Scale (RS-14), (Surzykiewicz et al., 2019), which will be used to measure this variable, has five dimensions, namely, equanimity, perseverance, self-reliance, meaningfulness, and existential aloneness. The short version of the RS test has been adapted to the Indonesian language. It has 14 items with a 7-point Likert scale (*r* = 0.87). The scale has good Construct Validity Fitness Indexes [Non Normed Fit Index (NNFI) = 0.99, Root Mean Square Error of Approximation (RMSEA) = 0.027, and Standardized Root Mean Residual (SRMR) = 0.026], (Valentino, 2021).

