### Data Analysis

Descriptive statistics will be used to describe relevant demographic data, such as the frequency and the percentage for the categorical data as well as the mean and the SD for the outcome measurements. There will be three analysis plans to prove the non-inferiority of the application, which are (1) repeated-measures ANOVAs (Goodman et al., 2016; Twisk et al., 2018), which will be used to test for differences between the TAU and the intervention groups (i.e., between-subjects factor) in the treatment at the four time points (i.e., within-subjects factor). We would like to assess whether the outcomes will be improved after treatment using the application and the TAU. An analysis will be conducted to check the constancy assumption. Then, both (2) the intention-to-treat (ITT) and (3) the per-protocol analysis will be performed. Previous studies showed that performing both analyses will produce more convincing results to conclude the non-inferiority of a new treatment (Hahn, 2012; Walker, 2019). The ITT analyses will be chosen to handle the missing value due to the protocol deviations, withdrawal, and non-compliance (Gupta, 2011) whereas the per-protocol analysis will minimize the factors that would make the two groups seem similar (Walker, 2019).

The statistical hypotheses in this non-inferiority trial use Δ. The null hypothesis states that the intervention using the application will be inferior to the TAU (H0: TAU–SAENA ≥ Δ). The alternative hypothesis states that the intervention will not be inferior (will have a similar effect) to the TAU although the effect may not be as good as the TAU within the extent of margin (H1: TAU–SAENA < Δ). Of note, 95% CI will be used. The interval will be the mean difference between the outcome measures of the two groups. The formula is as follows:

$$\begin{array}{l} \left(\mu_{saena}-\;\mu_{TAU}\right)\pm 1.96\sqrt{\frac{\sigma_{saena}^{2}}{n_{saena}}+\frac{\sigma_{TAU}^{2}}{n_{TAU}}} \end{array}$$

μ, mean; Tau, standard deviation; *n*, sample.

The 1.96 is the *z*-value, and the value from this formula can now be compared with Δ. If the interval remains above Δ, then the inferiority of the application will be proven according to the standards that have been set. In contrast, if the upper limit for treatment difference by the intervention group compared to the TAU group is < Δ, then the non-inferiority will be concluded.

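### SAENA students who stop before the third session have no defined end-of-treatment or 3-month assessment, while TAU students who stop early do, so the ITT comparison may be biased in a direction the protocol does not settle

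*Protocol article*

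**What the plan says.** The assessment schedule is in the Protocol article, Outcome Measurements. For the SAENA arm the last two points are listed as "4) at the end of the third counseling session (T3); and (5) 3 months after the third counseling session (T4". For the TAU arm, "the participants in the control group will be measured at 3–5 points in time depends on the number of counseling sessions they have", and the final point falls "3 months after the last session (TX". Three to five points means T0 and TX plus one to three post-session forms, so a single TAU session gives a full schedule.

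The Participants section deals with students who leave. Those who decline or "withdraw from the study will be followed up to identify their reasons for declining and withdrawing from the study". It says nothing about outcome forms for them, and it does not distinguish a student who stops counselling from one who leaves the study.

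The Data Analysis section then states: "The ITT analyses will be chosen to handle the missing value due to the protocol deviations, withdrawal, and non-compliance". A second analysis is to run beside it, because "the per-protocol analysis will minimize the factors that would make the two groups seem similar". The section presents the pair as more convincing together than either alone.

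**The concern.** Stopping early has different consequences in the two arms. In SAENA it removes the event from which T3 and T4 are dated. In TAU it only moves TX earlier. Followed literally, the schedule triggers no late outcome form for a SAENA student who stops after session 1 or 2.

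ITT defines whose outcomes are analysed and in which arm; it does not supply outcomes that were never collected. If SAENA's late data come mostly from students who finished three sessions, its ITT set at T3 and T4 lies close to its per-protocol set. Agreement between the two analyses then says less than the Data Analysis section expects of it. The comparison may also be biased, because selection by attendance acts on one arm more than the other. The margin is small (0.24 in Participants, 0.22 in the margin section), so a modest selective loss could matter.

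**Working it through.** **1. Which forms exist, by arm and sessions attended (Outcome Measurements, read literally)**

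| Sessions attended | SAENA | TAU |
|---|---|---|
| 0 | T0 | T0 |
| 1 | T0, T1 | T0, T1, TX |
| 2 | T0, T1, T2 | T0, T1, T2, TX |
| 3 | T0–T4 | T0–T3, TX |

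The arms differ in the rows for one and two sessions: TAU has a 3-month form there and SAENA has none. A student who attends no session has no dated final form in either arm.

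**2. The plan's own sample size**

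The inputs from Participants are SD 1, margin 0.24 and an 80% figure labelled as a CI, which I read as 80% power (assumption). With a true difference of 0 and one-sided 0.05 (also an assumption, since the level used is not stated):

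n = 2 × (1.645 + 0.842)² / 0.24² ≈ 214.7, so 215 per arm, as stated.

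The figure reproduces with no allowance for missing outcomes.

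**3. Bias from a comparison of those observed**

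Let d be the share of SAENA students without T3/T4, and x the number of SDs by which their outcome falls below that of SAENA completers. TAU is taken as fully observed. The completer mean exceeds the mean of all randomised SAENA students by d × x. The documents give neither d nor x, so the values below are assumed ranges.

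The false non-inferiority rate, when the true difference equals the margin, is Φ(d·x/SE − 1.96), with SE = √[1/(215(1−d)) + 1/215]. The 1.96 is the Data Analysis section's own value, so the nominal rate is 0.025. The rate is the same for either margin, because the true difference is set equal to the margin.

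| d | x (SD worse) | Bias toward SAENA (SD) | % of 0.24 | % of 0.22 | False non-inferiority rate |
|---|---|---|---|---|---|
| 10% | 0.25 | 0.025 | 10 | 11 | 0.044 |
| 10% | 0.5 | 0.05 | 21 | 23 | 0.073 |
| 20% | 0.25 | 0.05 | 21 | 23 | 0.071 |
| 20% | 0.5 | 0.10 | 42 | 45 | 0.163 |
| 30% | 0.25 | 0.075 | 31 | 34 | 0.105 |
| 30% | 0.5 | 0.15 | 62 | 68 | 0.292 |
| 20% | −0.25 (stoppers better) | −0.05 | −21 | −23 | 0.007 |

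Worked line for 20% and 0.5 SD: SE = √(1/172 + 1/215) = 0.102; 0.10/0.102 − 1.96 = −0.98; Φ(−0.98) ≈ 0.163.

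**4. When TAU also loses students**

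If TAU loses a share d′ with the same x, the net bias is (d − d′) × x. With x = 0.5:
- 20% against 10% gives 0.05 SD.
- 30% against 10% gives 0.10 SD.
- 20% against 20% gives 0.

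**The case against.** Three stronger readings are tempting, and the document does not support them.

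- **Withdrawers are followed only for their reasons.** The Participants sentence covers decliners and withdrawers together and concerns the recording of reasons. It does not say that outcome collection ends. It is also about leaving the study, and no rule is given for a student who stops sessions but stays in.
- **ITT becomes a completer analysis that cannot disagree with per-protocol.** Stoppers still contribute T0 and T1, and possibly T2. A missing-data method could be set in an analysis plan not shown. A per-protocol set could also exclude TAU deviators and other SAENA deviators.
- **The loss favours the app.** That needs stoppers to do worse than completers and TAU to lose fewer or less selectively. In brief solution-focused counselling some students may stop because they have improved, and the sign then reverses.

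Two further points have force. Study Design plans one session a week and lists the last assessment simply as after three months, so planned dates could be worked out. And the arm difference is not complete. A TAU student with one session has three forms and no T3, so a complete-case repeated-measures ANOVA "in the treatment at the four time points (i.e., within-subjects factor") would drop that student too. The contrast is sharpest for a stand-alone 3-month comparison, which the article does not name as primary.

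What remains is the stated schedule itself. Outcome Measurements, the more specific text, dates SAENA's T4 from the third session and TAU's TX from the last. An analysis plan may model the early forms, but it cannot recover late forms that were never triggered.

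**Conclusion.** The concern holds as a defect in the assessment schedule, not as a demonstrated bias toward the app. As written, SAENA students who stop after one or two sessions have no defined end-of-treatment or 3-month assessment, TAU students who stop early have a dated one, and ITT is relied on to cover the gap. SAENA's ITT result at T3 and T4 would rest largely on three-session completers, which weakens the check against the per-protocol analysis.

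The size and sign depend wholly on assumptions. With 20% stopping, a 0.5 SD deficit and TAU fully observed, the bias is 0.10 SD toward non-inferiority (42–45% of the margin), and the nominal 0.025 error becomes about 0.16. With 10% and 0.25 SD it is 0.025 SD, and the error is about 0.044. If stoppers do 0.25 SD better, 20% stopping gives 0.05 SD against SAENA. Equal and equally selective losses in TAU give no net bias. Because the sign is open and no stopping rate is documented, this should be fixed, but it is not a flaw that by itself invalidates the trial.

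**What to change.** In Participants, separate stopping counselling sessions from withdrawing consent for data collection, and state that only the latter ends the outcome forms.

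In Outcome Measurements, date the end-of-treatment and 3-month assessments in both arms from one origin that does not depend on attendance, for example randomisation. Redating SAENA alone would leave the arms on different clocks, because TX would still follow the last session of a need-based course. Ask every randomised student who still consents to complete the online forms at those dates, whatever the number of sessions attended.

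In Data Analysis, count these forms in the ITT set and use attendance only to define the per-protocol set. Drop the statement that ITT itself handles missing values.

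The cost is protocol wording, extra reminders to students who have stopped sessions, and some incomplete response. Since TAU sessions follow need, some TAU students may still be in counselling at the common end-of-treatment date, and the interpretation should say so. The change has to be made before data collection, because late forms not collected cannot be recovered afterwards.

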### Determining an Inferiority Margin of the Trial

In the non-inferiority trial, the researchers need to determine Δ (Hahn, 2012). In this study, the margin is the maximum acceptable extent of non-inferiority of the mobile-based counseling application. The maximum limit of Δ can be set to the entire effect size of the active control treatment (Hahn, 2012). Several proposals for choosing the inferiority margins in the context of SFBT have been made (Table 1). There are several suggestions for the maximum difference in outcomes that will be considered clinically irrelevant. It ranges from *d* = 0.17 to *d* = 1.76. The smallest margin was suggested by Schmit et al. (2016), (*d* = 0.24) for the treatment of internalizing disorders. Thus, in this study, it was decided to use the inferior margin of 0.22 (i.e., the inferior margin up to 0.22), corresponding to a small effect size.

**Table 1 T1:** The effect size from the solution-focused brief therapy (SFBT)-related studies.

**Previous studies**	**Effect size**
Impacts on academic and emotional difficulties (Daki and Savage, 2010)	≈0.13 (partial eta squared, medium effect size)
Meta-analysis of solution-focused brief therapy for treating symptoms of internalizing disorders (Schmit et al., 2016)	≈0.24 (Hedges' g, small effect size)
Examining the effectiveness of solution-focused brief therapy: a meta-analysis (Kim, 2008)	0.26–0.38 (Cohen's *d*, small effect size)
SFBT for health-related psychosocial outcomes (Zhang et al., 2018)	0.34 (Cohen's *d*, small effect size)
Solution-focused brief therapy in schools: A review of the outcome literature (Kim and Franklin, 2009)	0.38–1.76 (Cohen's *d*, medium to large effect size)

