As mentioned earlier that this kind of trial needs to have a large number of participants to ensure that the statistical power is sufficient to differentiate the two groups (Hahn, 2012). This study might be able to have the ideal number of participants due to limited resources. However, since the application-based counseling is assumed to be more practical for the young generation, based on the previous studies, we aimed for a small effect size, so the number of participants in this study might be limited but not underpowered.

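### The 215 per arm fits 80% power only at a one-sided 5% level; under the stated 95% CI power is about 70% (Δ = 0.24) or 63% (Δ = 0.22) if the two treatments are equal

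*Protocol article*

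**What the plan says.** All of this is in the protocol article.

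- **Participants** gives the inputs: "With 80% CI, the expected SD will be one, and the inferiority margin (Δ) will be 0.24". It then gives the result: "the number of participants per arm needs to be 215 and the total sample size needs to be 430". It names no significance level and does not use the word power. Just before the calculation it remarks that fewer participants suffice if the new intervention is assumed to be slightly better, but it gives no figure for such an advantage.
- **Determining an Inferiority Margin of the Trial** settles on another value: "it was decided to use the inferior margin of 0.22 (i.e., the inferior margin up to 0.22), corresponding to a small effect size".
- **Data Analysis** fixes the test: "Of note, 95% CI will be used". The interval formula uses 1.96, and the text adds: "The 1.96 is the *z*-value, and the value from this formula can now be compared with Δ". Non-inferiority is concluded from one limit of that interval.
- **Discussion** assures the reader that "the number of participants in this study might be limited but not underpowered".

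**The concern.** A sample size and the test it supports must share the same error level. Here the sample size is attached to an 80% interval and the analysis to a 95% interval, and no α or power is given to connect them. If 215 came from a more lenient test than the one that will be run, the trial has less chance of showing non-inferiority than its readers are led to expect.

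At stake is a trial of 430 students that could fail to show non-inferiority even though the application is as good as usual treatment. The Discussion's statement on power would then not follow from the trial's own decision rule.

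**Working it through.** **Inputs.** SD = 1, Δ = 0.24 and n = 215 per arm (Participants); Δ = 0.22 (margin section); z = 1.96 with one limit compared with Δ, so one-sided α = 0.025 (Data Analysis). The true difference is not stated and is taken as 0. All 215 per arm are taken as analysed.

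**Formulas** (SD = 1, true difference 0):

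- n per arm = 2 × (z for 1 − α + z for power)² / Δ²
- power = Φ(Δ / √(2/n) − z for 1 − α)

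**Step 1: reproduce 215.** At Δ = 0.24, Δ² = 0.0576.

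| Reading | Calculation | n per arm |
|---|---|---|
| Literal 80% CI (one-sided 0.10), 80% power | 2 × (1.2816 + 0.8416)² / 0.0576 | 156.5, so 157 |
| Literal 80% CI, 90% power | same formula with 1.2816 for power | 229 |
| One-sided 0.05, 80% power | 2 × (1.6449 + 0.8416)² / 0.0576 | 214.7, so **215** |
| One-sided 0.025, 80% power | 2 × (1.9600 + 0.8416)² / 0.0576 | 272.5, so 273 |
| One-sided 0.025, 70% power | 2 × (1.9600 + 0.5244)² / 0.0576 | 214.3, so **215** |

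Two readings give 215. The printed 80% points to the first of them, one-sided 5% with 80% power. The other, one-sided 2.5% with 70% power, is the same shortfall seen from the other side. A literal 80% interval gives 215 at neither 80% nor 90% power.

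**Step 2: power under the stated analysis.** √(2/215) = 0.09645.

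- Δ = 0.24: 0.24 / 0.09645 = 2.488; 2.488 − 1.960 = 0.528; Φ(0.528) = **70.1%**.
- Δ = 0.22: 0.22 / 0.09645 = 2.281; 2.281 − 1.960 = 0.321; Φ(0.321) = **62.6%**.

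A check with the noncentral t distribution gives 69.9% and 62.4%.

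**Step 3: separate the two causes.** At one-sided 5% and Δ = 0.24, power is 80.1%. Moving to z = 1.96 lowers it to 70.1%, a loss of 10 points that belongs to this point. Moving the margin to 0.22 takes it to 62.6%, a further 7.5 points that belong to the margin conflict.

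**Step 4: what would give 80% under the 95% CI.**

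- By size: 273 per arm (546 in total) at Δ = 0.24, or 2 × (2.8016)² / 0.0484 = 324.3, so 325 per arm (650 in total), at Δ = 0.22. Both are before any dropout.
- By assumption: the distance needed is 2.8016 × 0.09645 = 0.270 SD. With 215 per arm the application would have to be truly better by 0.270 − 0.24 = 0.03 SD, or 0.270 − 0.22 = 0.05 SD.

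**Step 5: the alternative of a one-sided 5% test (90% CI, z = 1.645).** With 215 per arm, power is 80.1% at Δ = 0.24 and Φ(2.281 − 1.645) = Φ(0.636) = 73.8% at Δ = 0.22, where 256 per arm would be needed for 80%.

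**The case against.** **The 5% level and the 80% power are inferred.** This is correct. A reader might infer that 215 proves a one-sided 5% design, but it does not, because 2.5% with 70% power also gives 215. The power figures in step 2 do not depend on that inference. They use the stated n, SD, margins and z, plus a zero true difference.

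**A small true advantage would restore 80%.** This also stands as arithmetic: 0.03 or 0.05 SD in favour of the application is enough. The article raises the possibility but puts no figure on it. The advantage it describes is practicality, and Study Design says the application is not meant to be the more effective treatment. The near-exact match at zero difference suggests that no advantage was used. So this does not rescue the plan, but it means the trial cannot be called underpowered without the condition of zero difference.

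**Attrition.** A reader might infer a further defect because no dropout allowance appears. The documents do not support that: they give no dropout rate, and a condensed article may leave the allowance to the full protocol. The figures here are simply before any loss.

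**The Discussion's reasoning.** It is tempting to say that it argues from a small effect size to a smaller sample, which would be backwards. The passage is too unclear to carry that charge, since it also leans on practicality. Only its conclusion on power is at issue.

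**Baseline adjustment.** A reader might expect it to recover the lost power for nothing. The gain depends on the correlation between baseline and outcome, which the documents do not give.

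**Conclusion.** The point holds. The reference to an 80% confidence interval is wrong as written: taken literally it does not yield 215 at 80% power, and it disagrees with the 95% CI of the analysis. Under the stated analysis, with SD 1, zero true difference and 215 analysed per arm, power is about 70% at Δ = 0.24 and about 63% at Δ = 0.22. If the treatments are equal, the chance of failing to show non-inferiority is therefore about 30% (1 − 0.701) or 37% (1 − 0.626), where 80% power would imply 20%. The 37% combines this mismatch with the margin conflict and should not be attributed to the mismatch alone.

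The statement that the trial is adequately powered is unsupported unless a true advantage of about 0.03 SD (Δ = 0.24) or 0.05 SD (Δ = 0.22) is assumed and stated.

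A reader might also infer that the mismatch makes a false claim of non-inferiority more likely. It does not: the 95% CI is the stricter of the two rules, so the harm is lost power only.

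**What to change.** 1. In Participants, replace the reference to an 80% CI with the one-sided α, the power and the assumed true difference.
2. Use one margin, 0.24 or 0.22, in every section.
3. Keep the 95% CI in Data Analysis and restate the power of 430 participants as about 70% (Δ = 0.24) or about 63% (Δ = 0.22), at zero true difference and before any dropout.
4. Remove the assurance of adequate power from the Discussion. If the sponsor relies on a small true advantage, state its size and justify it.

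If a one-sided 5% test is what the sponsor intends, Data Analysis must say so and use a 90% CI with z = 1.645. That choice restores 80% only at Δ = 0.24; at Δ = 0.22 power is about 74%.

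The cost is a change of text and a less favourable power figure. No added participants are required. Enlarging to 546 or 650 would be an alternative, but the article reports 482 clients at the centre in 2020, so 430 is already 430/482 = 89% of a year's intake.

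### The 215 per arm fits a one-sided 5% test at margin 0.24; under the planned 95% CI, power with no true difference is about 63% (margin 0.22) or 70% (margin 0.24)

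*Protocol article*

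**What the plan says.** All references are to the protocol article.

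- **Participants** gives the sizing inputs: "With 80% CI, the expected SD will be one, and the inferiority margin (Δ) will be 0.24". The result is: "It was calculated that the number of participants per arm needs to be 215 and the total sample size needs to be 430". No alpha is named and no number is given for the true difference. The nearest statement is a general conditional: "if the new intervention is assumed to be slightly more effective than the TAU, the number of samples can be reduced".
- **Determining an Inferiority Margin of the Trial** settles on a different margin: "it was decided to use the inferior margin of 0.22".
- **Data Analysis** fixes the test: "Of note, 95% CI will be used". The printed formula is the unadjusted difference of two means plus or minus 1.96 standard errors. Non-inferiority is concluded if the upper limit is below the margin. Inferiority is concluded only if the whole interval lies above it.
- **Discussion** says of the sample size that "the number of participants in this study might be limited but not underpowered".

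**The concern.** The sizing statement, the margin decision and the analysis rule should describe one test, and they do not. The margin is 0.24 in one section and 0.22 in another. The only confidence level in the sizing statement is 80%, while the analysis uses 95%. If 215 per arm was derived for a more lenient test than the one to be run, the trial has less power than its authors believe, and the reassurance in the Discussion has no basis.

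What is at stake is the chance of an inconclusive trial. With too few participants, an application that is truly as good as TAU will often fail to show it.

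**Working it through.** **Inputs.** From Participants: SD 1, margin 0.24, 215 per arm. From the margin section: margin 0.22. From Data Analysis: z = 1.96. Two inputs are assumptions: the 80% is read as power (z = 0.8416), and the true difference is zero unless stated otherwise.

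**Step 1: reproduce 215.** With no true difference, n per arm = 2(z_α + z_β)²/Δ².
- One-sided 5%, Δ 0.24: 2(1.645 + 0.8416)²/0.24² = 214.7, so 215. This matches.
- One-sided 2.5%, Δ 0.24: 2(1.96 + 0.8416)²/0.24² = 272.5, so 273. No match.
- One-sided 5%, Δ 0.22: 256. One-sided 2.5%, Δ 0.22: 324.3, so 325. No match.
- A literal 80% CI (z = 1.2816) with 80% power, Δ 0.24: 156.5, so 157. No match.

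Of these settings, only one-sided 5% with Δ 0.24 gives 215. It corresponds to a 90% CI, which the plan does not use.

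**Step 2: power under the planned test.** SE = √(2/215) = 0.0964. Power = Φ(Δ/SE − z).

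| Test | Δ 0.22 | Δ 0.24 |
|---|---|---|
| 95% CI, z = 1.96 | Φ(2.281 − 1.96) = 62.6% | Φ(2.488 − 1.96) = 70.1% |
| One-sided 5%, z = 1.645 | 73.8% | 80.1% |

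A noncentral t calculation gives 62.4% and 69.9% for the first row. So with truly equal treatments, non-inferiority is missed with probability 37% (Δ 0.22) or 30% (Δ 0.24). Even at one-sided 5%, the 0.22 margin alone costs about six points of power.

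**Step 3: what a miss means.** The CI half-width is 1.96 × 0.0964 = 0.189. Non-inferiority therefore needs an observed shortfall below 0.22 − 0.189 = 0.031 SD, or 0.24 − 0.189 = 0.051 SD. A conclusion of inferiority needs an observed shortfall above 0.22 + 0.189 = 0.409 SD, or 0.24 + 0.189 = 0.429 SD. Anything in between is inconclusive.

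**Step 4: sensitivity to the true difference.** Let b be the true SAENA minus TAU difference in SD units, with higher scores better. In the TAU − SAENA direction of H0 and H1, power = Φ((Δ + b)/SE − 1.96). For 80%, Δ + b must equal (1.96 + 0.8416) × 0.0964 = 0.270. So b must be 0.05 SD (Δ 0.22) or 0.03 SD (Δ 0.24). If the application is truly worse by 0.02 to 0.05 SD (an assumed range), power falls to 55–42% (Δ 0.22) or 63–50% (Δ 0.24).

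The interval in Data Analysis is printed as SAENA − TAU. If its upper limit is compared with Δ literally, the sign of b reverses: a benefit of 0.05 SD on coping self-efficacy would lower power to Φ((0.22 − 0.05)/0.0964 − 1.96) = 42%. The zero-difference figures in Step 2 are the same in both directions.

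**The case against.** **A small benefit may have been assumed.** This is the strongest reply. Participants notes that sample size can be reduced if the new intervention is slightly better, and only 0.03 to 0.05 SD is needed to restore 80%. That is modest, and the documents do not rule it out. Neither the Study Design remark that the application is not meant to outperform usual treatment nor the wording of H1 ("the effect may not be as good as the TAU within the extent of margin") contradicts it: the first explains the choice of design, and the second is true of any non-inferiority alternative. But the benefit appears only as a conditional, no size is given, and the support offered is practicality and access, not an effect on coping self-efficacy. A benefit can also be solved for to make almost any alpha and margin yield 215, so the match is no evidence that one was used.

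**The analysis may be more efficient than the formula.** Repeated-measures ANOVA is among the planned analyses. If the primary comparison were baseline-adjusted, a baseline correlation of about 0.58 (Δ 0.22) or 0.46 (Δ 0.24) would restore 80%. The documents give no correlation, and the printed decision rule is unadjusted. It does follow that the 63% and 70% figures must be labelled as applying to the unadjusted comparison.

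**The article is condensed.** The missing alpha and true difference may stand in a fuller protocol, so their absence alone carries little weight. The conflict between printed margins, and between the sizing and the printed test, does not depend on it.

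**The adequacy claim is hedged.** The Discussion mentions limited resources and says numbers might be limited. It still asserts adequate power.

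**A stronger reading to avoid.** A reader might infer that a narrow miss would be declared evidence that the application is inferior. Data Analysis does not support this: inferiority requires the whole interval to lie above the margin, and an interval that straddles it gives neither conclusion.

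**Conclusion.** The point holds. With no true difference, 215 per arm fits a one-sided 5% test at margin 0.24 with 80% power. The plan tests with a 95% CI and decides on a margin of 0.22. Under its own test the power is about 63% (Δ 0.22) or 70% (Δ 0.24), so the Discussion's adequacy claim is not supported. The practical consequence is a 37% or 30% chance of an inconclusive result when the treatments are equally effective, against an apparent 20%.

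This rests on SD 1, full data on 215 per arm, the unadjusted two-mean interval, zero true difference and reading the 80% as power. Dropout would lower the figures; an assumed benefit or an effective baseline adjustment would raise them.

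A reader might go further and infer that 215 is an arithmetic error or that the trial cannot succeed. Neither follows: the number is right for a different test, and a small true benefit would bring power to 80%.

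**What to change.** Keep 215 per arm and the 95% CI, and change the text.

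1. **Participants.** Replace the 80% CI with the intended power, if that is what was meant. State one-sided alpha 2.5% to match the 95% CI, and state the assumed true difference. Use one margin here and in the margin section: 0.22, which that section decides on, unless the sponsor confirms 0.24.
2. **Discussion.** Replace the adequacy claim with the power under the planned test: about 63% if the treatments are equally effective (70% if the margin is 0.24), for the unadjusted comparison.
3. **If a benefit of the application was assumed**, give its size and basis. In the TAU − SAENA direction, 80% needs 0.05 SD (Δ 0.22) or 0.03 SD (Δ 0.24). Write the CI formula in Data Analysis in that same direction, so that the limit compared with the margin agrees with H0 and H1.

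The cost is a less favourable stated power; treatment, visits and sample size do not change. Two costlier routes are not requested. Restoring 80% at zero difference would need 546 participants (Δ 0.24) or 650 (Δ 0.22). Participants reports that "The center admitted 482 clients in that year, with an average of 40 clients per month". Even if every client were eligible and consented, recruitment would take 546/40 = 13.7 or 650/40 = 16.3 months, against 430/40 = 10.8. Moving to a 90% CI would restore 80% only at Δ 0.24 and would double the one-sided error from 2.5% to 5%.
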